### Randomisation

Eligible participants will be randomised into the CBT+ or TAU+ group using a complete randomisation scheme generated in advance. Specifically, block sizes of variable size (4, 6 or 8) will be used. Random seeds will be generated to ensure allocation concealment and prevent pre-guessing of the allocation sequence at the end of each block. Randomisation will be stratified by baseline Insomnia Severity Index (ISI) scores (≤7, ≥8) and cancer stage (≤2, ≥3). The randomisation scheme was generated and setup in REDCap (Research Electronic Data Capture) by a member of the research staff (BB) who is not involved in recruitment or delivery of intervention and is not the principal investigator. All participants will receive a random identification number, which will be used to link data from the different assessments. All direct identifiers (for example, name, address and telephone numbers) will be stored separately.

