### Sample size and power

Based on previous studies of CBT for insomnia and sleep in people with cancer and BLT [69–74] we expect a moderate to large effect size for both primary outcomes. Given that our combined CBT+ targets multiple and different mechanisms of change, we expect larger effects than shown in previous studies utilising only CBT or BLT. Specifically, we expect a standardised mean difference of *d* = 0.70, corresponding to a medium-to-large between-group effect at the post-treatment assessment.

Power analyses based on an independent samples *t* test showed that a total of 70 women will provide >80% power to detect a standardised mean difference of 0.70 at post-treatment, assuming α = 0.05 and equal variance between groups. Power analyses are not readily available for latent growth models (LGMs) and require complex simulations. Therefore, we chose power analysis based off a *t* test as a conservative estimate as, due to randomisation, no baseline differences between conditions are expected so the difference in the slopes from LGMs between treatment and control will be based on post-treatment mean differences but should have lower variability because of removing variability due to individual differences at baseline. Thus, we anticipate the LGMs will have more power than a *t* test based on post-treatment scores and that our power estimates are conservative, although final power will depend on the difference, variability, and correlations in data over time, which are unknown. We will continue recruitment until we reach 70 completers. Progress to date is shown in Fig. 1.

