#### Baseline comparisons

Participant characteristics at baseline will be presented by treatment group, and statistical tests will be conducted to verify that randomisation was successful. Discrete variables will be summarised by frequencies and percentages, and baseline group differences tested using chi-square tests. Continuous variables will be summarised using mean (standard deviation) or median (interquartile range) and baseline group differences, tested using independent *t* tests or Wilcoxon signed-rank tests for variables that evidence non-normal distributions. If there are significant differences in any participant characteristics at baseline, the variable(s) will be included as covariates in the final analyses.

#### Aim 1

Aim 1 is to test the efficacy of CBT+ compared to TAU+ for improving symptoms of sleep disturbance. Aim 1 will be tested using LGMs. LGMs will be estimated with an intercept and two linear slopes, representing a piecewise model. Slope 1 will have loadings constrained to 0, 0.5, 1.0 and 1.0 for weeks 0, 3, 6 and 12, respectively, capturing the linear change from baseline (week 0) to post-intervention (week 6). Slope 2 will have loadings constrained to 0, 0, 0 and 1.0 for weeks 0, 3, 6 and 12, respectively, allowing a different slope from post-intervention (week 6) to follow-up (week 12) compared to from baseline (week 0) to post-intervention (week 6). The means and variances of the intercept and slope factors will be freely estimated (corresponding to random effects in linear mixed models) and the intercept and slope covariances will be estimated. The residual variance will be constrained to equality across time and residuals assumed uncorrelated, corresponding to an independent, homogenous residual structure. Intercepts of indicators will be constrained to 0 to allow estimation of the latent random intercept mean.

There are two stratification factors: screening ISI (≤7, ≥8) and cancer stage (≤2, ≥3). These factors will be crossed, creating four groups: early-stage, low ISI; advanced-stage, low ISI; early-stage, high ISI; and advanced-stage, high ISI. Dummy codes will be created for each strata, with early-stage, low ISI treated as the reference group. These dummy codes will be included as covariates to adjust for their effect on the random intercept following recommendations that stratification factors be adjusted for in analyses of randomised controlled trials [76, 77].

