Aim 3 is to explore potential mechanisms of CBT+ and moderators of the intervention efficacy. Mechanisms (i.e. pre-sleep arousal, beliefs and attitudes about sleep, vulnerability to insomnia under stress and intrusive thoughts before bed) will be tested using mediation conducted in path analyses. Specifically, we will examine the effect of condition on change in mechanisms (for example, pre-sleep arousal) from baseline to treatment mid-point, and test whether the change in mechanisms from baseline to treatment mid-point accounts for the condition effects on change in outcomes (for example, ISI) from baseline to post-treatment and follow-up. Statistical mediation will be determined by evaluating the indirect effects, calculated as the product of the paths from condition to change in mechanisms and from change in mechanisms to change in outcomes. Bootstrapping will be used to estimate the confidence interval for indirect effects and their statistical significance. Given the modest sample size, analyses will be conducted for each mechanism and outcome individually.

Treatment moderators (i.e. pain, chronotype, perceived credibility and expectations of the intervention, and adherence to the intervention protocol) will be evaluated by modifying the primary linear mixed effects analyses from aims 1 and 2 to include a condition × moderator interaction, along with all lower order effects predicting slope 1 and slope 2 of the piecewise model. Individual moderators will be tested in separate models.

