## Trial status

Recruitment commenced in July 2018 and was completed in October 2019. One hundred and one women have been recruited and randomised to date (see Fig. 1). It is anticipated that all 3-month follow-up data will be collected by January 2020. This is protocol version number 7, 18 November 2019.

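### The stratification codes adjust only the intercept, and baseline ISI is not among the moderators, so no planned analysis gives the slope-1 effect in women with ISI ≥8

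*Protocol article*

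**What the plan says.** **Entry.** The inclusion criteria (Screening) set no minimum ISI and require no sleep complaint. Low scorers are expected, because the Randomisation section states: "Randomisation will be stratified by baseline Insomnia Severity Index (ISI) scores (≤7, ≥8) and cancer stage (≤2, ≥3".

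**Model.** Under Statistical analyses, Aim 1, the two stratifiers are crossed into four groups and dummy coded: "These dummy codes will be included as covariates to adjust for their effect on the random intercept". Treatment predicts slope 1 and slope 2, with its effect on the intercept fixed at zero. The single treatment effect on slope 1 is named as the primary result. Intercept and slope covariances are estimated. Aim 2 uses the same model.

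**Moderators.** Aim 3 gives a closed list: "Treatment moderators (i.e. pain, chronotype, perceived credibility and expectations of the intervention, and adherence to the intervention protocol". Each is tested through a condition × moderator term on both slopes. Neither baseline ISI nor its stratum appears there or in the Aims and hypotheses section.

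**Power.** The expected effect is introduced as "Based on previous studies of CBT for insomnia and sleep in people with cancer and BLT", and the claim is that "a total of 70 women will provide >80% power to detect a standardised mean difference of 0.70 at post-treatment". The calculation uses a 5% significance level and takes the variance to be the same in both arms.

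**The concern.** The strata are adjusted for at the starting level, while the primary result is a rate of change. One stratifier is a cut of baseline ISI, and change in ISI is a primary outcome. Women who start low have little room to fall and women who start high have more, so equal mean slopes across strata within an arm is a strong restriction. The estimated intercept-slope covariance does not lift it: once the intercept is regressed on stratum, that covariance describes residual variation and leaves the stratum mean slopes equal.

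The second matter is what can be reported. The Abstract and Discussion expect the results to inform treatment of both sleep disturbance and insomnia. The enrolled women span both sides of the ISI cut, and the plan yields one average over them. A reader asking what CBT+ does for women who start with ISI ≥8 will find no planned estimate. The statisticians are unblinded, so an ISI ≥8 analysis added later would be open to the charge that it was chosen after seeing the data.

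**Working it through.** **1. The plan's own power figure.** Inputs from Sample size and power: 70 women, d = 0.70, α = 0.05, independent-samples t test. Two-sided testing and 35 per arm are assumed. Noncentrality = 0.70 / √(1/35 + 1/35) = 2.93 on 68 df, giving power of 82.3%. The stated figure of over 80% reproduces.

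**2. What that figure needs.** It holds if 0.70 applies to everyone enrolled. Let s be the share with ISI ≤7 and f the effect in that stratum as a fraction of 0.70, with the SD held at 1:

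pooled d = 0.70 × [(1 − s) + f·s]

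For example, s = 20% and f = 0 gives 0.70 × 0.80 = 0.56. The document states neither s nor f; both are assumed.

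| s | pooled d, f = 0 | power, 70 women | pooled d, f = 0.5 | power, 70 women |
|---|---|---|---|---|
| 10% | 0.63 | 74% | 0.665 | 78% |
| 20% | 0.56 | 64% | 0.63 | 74% |
| 30% | 0.49 | 52% | 0.595 | 69% |
| 40% | 0.42 | 41% | 0.56 | 64% |
| 50% | 0.35 | 30% | 0.525 | 58% |

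If all 101 randomised women contributed, which is an upper bound, power at f = 0 would be about 80%, 68% and 55% for s = 20%, 30% and 40%. The nearest figure in the document is in the Discussion: 33 of 219 women approached (33/219 = 15%) reported no sleep complaints. That is not an ISI count among randomised women.

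**3. What intercept-only adjustment does.** A mixed model was simulated with treatment constrained to zero at baseline, one ISI stratifier and visits at weeks 0, 3 and 6. All inputs were assumed: 400 women, 30% with low ISI, mean ISI 5 and 14, SDs of 2.5 (intercept), 3 (slope) and 2 (residual), control-arm change of +1 (low) and −3 (high), treatment effect of 0 (low) and −4 (high), 60 runs. The true average effect is 0.7 × (−4) = −2.80.

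- Stratum on the intercept only: mean estimate −2.84, SE 0.47.
- Stratum on the slope as well: mean estimate −2.84, SE 0.40.
- Treatment × stratum on the slope added: −4.06 in the high stratum, with a difference of 4.08 for the low stratum.

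So there is no bias to speak of. Precision is lost: 0.471/0.405 = 1.16. These inputs are strong. The low stratum changes by +1 in both arms and the high stratum by (−3 − 7)/2 = −5 on average, a gap of 6 points. A simulation at N = 101 with other assumed inputs put the excess SE at about 2–8%.

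The second and third results are distinct. A stratum-to-slope path improves precision but still returns one pooled effect; only the treatment × stratum term separates the groups.

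**4. What the added analysis could deliver.** At N = 101 and s = 30%, the ISI ≥8 stratum has 0.7 × 101 = 70.7 women. The 95% CI half-width is 1.96 × √(4/70.7) = 0.47 SD for its effect and 1.96 × √(4/30.3 + 4/70.7) = 0.85 SD for the interaction. Power to detect d = 0.70 within ISI ≥8, for s = 20% to 50%, is 73% down to 52% with 70 women and 87% down to 68% with 101. Power for the interaction (0.70 against 0) over the same range is 21% to 30% with 70 women and 29% to 41% with 101.

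**The case against.** The broad population is deliberate. Aim 1 concerns symptoms of sleep disturbance in women on chemotherapy, and the Background argues that disturbance short of clinical insomnia still does harm. ISI is a primary outcome, so the pooled slope-1 effect is a legitimate average effect on insomnia symptoms in the women enrolled. This stands. A reader might infer that the trial cannot say whether CBT+ treats insomnia, or that it mixes prevention with treatment. The document supports neither: it states no prevention aim and does not define ISI ≤7 as absence of relevant insomnia.

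A reader might also blame the intercept-only covariates for the pooling. They do not cause it, as step 3 shows. Nor does regression to the mean bias the comparison: with randomisation stratified on ISI it is equal across arms in expectation.

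The power loss is conditional. It needs an unstated share and an effect that is smaller at ISI ≤7, and the populations behind d = 0.70 cannot be seen here. The limited room to improve is argued for ISI only, not for sleep efficiency. Cancer stage is also a stratifier and also absent from the moderators, so ISI is not uniquely neglected; its particular claim is that it is the baseline of a primary outcome.

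Further subgroup analyses are often left to a fuller document. That has less force here, because the article fixes the model paths and closes the moderator list.

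**Conclusion.** The concern holds in a limited form, as an improvement that should be made and not as a fault that invalidates the primary analysis. The strata act on the intercept while the primary result is a slope. The cost is precision: 2–8% on the SE in one assumed setting and 16% in a stronger one, with no bias found. No planned analysis gives the effect at ISI ≥8, although the strata are recorded and the existing moderator template would take ISI unchanged. The power statement is arithmetically right but rests on d = 0.70 for the whole enrolled sample. Any shortfall depends on the ISI ≤7 share and the effect in that stratum, neither of which the document gives.

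**What to change.** - In the Aim 1 and Aim 2 models, let the stratum codes predict slope 1 and slope 2 as well as the intercept, with the corresponding stratum-by-time terms in the sleep-efficiency model.
- Add baseline ISI, continuous or by stratum, to the Aim 3 moderators using the existing condition × moderator template, labelled exploratory.
- Report the ISI ≥8 slope-1 effect with its confidence interval beside the pooled effect, which stays primary, and tie any statement specific to women with insomnia to that estimate.
- State that the power calculation assumes d = 0.70 across the whole enrolled sample, and report the share with ISI ≤7.
- Use one name for the stratifier: Randomisation calls it baseline ISI, Aim 1 calls it screening ISI.

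The cost is a few lines of model code and one table, with no new data. The downside is a less precise within-stratum estimate and a weak interaction test (about 21–41% power under the assumptions above), so a non-significant interaction should not be read as evidence of equal effects.

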### Data storage and confidentiality

All participants will receive a random identification number which will be used to link data from the different assessments. Coding all participant data with a unique identification number will minimise the risk of loss of confidentiality. The only dataset with participant identifier information will be the participant tracking system used to follow-up and contact women. All other datasets will label participant records with a unique study number and be stripped of other identifying information; specifically, clinical data will not reside with identifying data. Survey data will be kept in locked files or password-protected data files. All results will be described in aggregate without identification of individual women. Study investigators will have access to the final dataset.

### Ethics approval and safety monitoring

The study has received ethics approval from the PMCC Human Research ethics committee, protocol number 17/159. Governance and oversight of the trial will be monitored by two committees, the Steering Committee and the Data and Safety Monitoring Board (DSMB). The Steering Committee comprises the study investigators and a consumer representative. The DSMB comprises two independent researchers, a consumer representative, and two members of the study investigator team. The DSMB will be responsible for monitoring participant safety, data quality, and implementation of the protocol. If any women report severe symptoms of sleep disturbance, depression, or anxiety, we will inform their clinical team and recommend that they seek a referral to a sleep specialist or clinical psychologist. Any women with previously undiagnosed severe psychiatric conditions identified during screening will also be informed and recommended to seek a referral to psychiatry or clinical psychology. A description of all undesirable and unanticipated events during the intervention phase (adverse events) will be recorded on Qualtrics. As this trial is minimally funded, there is no independent audit. Any protocol modifications will be communicated to the Human Research ethics committee and participants by the study team. No serious harm is expected as a result of the trial. However, if harm does occur, the primary sponsor and Monash University insurance will cover care for research participants.

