**Method/design:**

Women diagnosed with breast cancer who receive intravenous chemotherapy treatment at a quaternary referral metropolitan cancer centre in Melbourne, Australia, will be recruited. Recruitment will occur after diagnosis and prior to completion of chemotherapy. Eligible women will be randomised to the combined CBT and BLT intervention (CBT+) or relaxation audio-enhanced treatment as usual (TAU+). The CBT+ group will receive one face-to-face session on sleep strategies, one subsequent telephone call, and seven email packages containing CBT-based information and strategies. CBT+ participants will also wear Luminette® light glasses for 20 min each morning for the 6-week duration of the intervention. Women in TAU+ will receive two relaxation audio tracks via email. Outcomes will be measured at multiple points throughout the 6 weeks. Primary outcomes will be symptoms of insomnia and sleep efficiency, measured using the Insomnia Severity Index and a self-reported sleep diary. Secondary outcomes include objective measures of sleep assessed using the ActiGraph wGT3X-BT, and sleep-related complaints, fatigue and mental health, all assessed using the Patient-Reported Outcomes Measurement Information System (PROMIS). Data will also be collected on potential treatment moderators and mechanisms and adherence to treatment. There will be 3-month follow-up measurements of insomnia symptoms, fatigue, sleep-related impairment, sleep disturbance, depression and anxiety.

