#### Light therapy

Bright light is one of the strongest cues for circadian timing; in addition, it has an alerting effect and can reduce fatigue [33], a common symptom particularly following chemotherapy [34]. Bright light therapy (BLT) is a simple form of treatment with relatively low costs, and its efficacy in treating circadian disruption has been well documented [33, 35–37]. Although BLT is effective in a range of populations presenting with insomnia, disturbed sleep or fatigue, there are no guidelines to date for the use of BLT for specific sleep complaints or clinical populations. There is consensus in research regarding the timing of BLT treatment [33]. Exposure to BLT around habitual waking time may shift the circadian rhythm earlier, whereas BLT in the biological evening could shift the circadian rhythm later. BLT has its greatest effect on circadian rhythms immediately before or after the temperature nadir (the lowest point the core body temperature falls to overnight, typically between 4 and 6 a.m.) [33]. Thus, BLT in the morning should ideally occur early, without forcing individuals to wake too early resulting in daytime sleepiness.

Despite the evidence for circadian disruption among women with BC and the efficacy of BLT, few studies have investigated BLT in this population. Ancoli-Israel and colleagues [38] tested BLT to prevent fatigue in women undergoing chemotherapy. In their study, the BLT protocol consisted of placing a 10,000 lux light box approximately 45 cm from the participant’s head within a 45° angle from the midline of the visual field. The light box was used for 30 min each morning on awakening throughout the first four cycles of chemotherapy. This intervention was effective in preventing women from experiencing fatigue during chemotherapy [38]. In the same study, BLT also protected women from circadian disruption during chemotherapy [26]. Redd and colleagues [39] utilised the same BLT protocol for 4 weeks in a sample of BC survivors, and found that BLT significantly improved cancer-related fatigue. Similar findings were previously reported by Liu and colleagues [40]. However, despite the promising evidence, there is little evidence on whether BLT improves sleep, not just fatigue, during chemotherapy for BC.

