### Screening

Further eligibility will be assessed via structured interviews designed to detect sleep disorders or severe psychiatric disorders. Sections of the Mini International Neuropsychiatric Interview (MINI) [50] will be administered, including those relating to major depressive disorder (module A), generalised anxiety disorder (module N), manic and hypomanic episodes (module C), alcohol dependence and abuse (module I), substance dependence and abuse (module J), current post-traumatic stress disorder not related to cancer experiences (module H), and psychotic disorders (module K). The Duke Structured Interview for Sleep Disorders [51] will be administered in its entirety. A detailed risk management protocol was used to ensure that if previously unidentified disorders were found, women were referred to psychology, psychiatry or sleep clinics, as appropriate.

Inclusion criteria are: women diagnosed with any stage of primary BC; over 18 years of age; receiving intravenous chemotherapy, with or without radiotherapy, during the study period; able to provide informed consent; able to understand and speak English; able to regularly receive and access emails; able and willing to wear light therapy glasses.

Exclusion criteria are: male; receiving neo-adjuvant chemotherapy; diagnosed with a severe psychiatric disorder or severe substance use disorder as identified through the MINI; having a history of migraines. Individuals with very advanced sleep timing, defined as a habitual bedtime before 8 p.m. and rise time before 4 a.m. or delayed sleep timing defined as habitual bedtime after 3 a.m. and rise time after 11 a.m., or irregular or non-24 sleep and wake pattern will be excluded, based on the Duke structured sleep interview.

It is possible that eligible participants will be receiving additional treatment for sleep complaints (for example, psychological treatment, prescribed sleep medication, herbal remedies, and so forth). These participants will not be excluded; however, this information will be obtained via self-reports and medical record extraction and will be adjusted for in sensitivity analyses. Involvement is voluntary, and participants may withdraw from the study at any time. Involvement will not impact participants’ care and their medical treatment will continue as usual.

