##### Light therapy individualised protocol

The light therapy component will consist of daily use of light glasses for the 6-week duration of the intervention. Participants will receive a pair of Luminette® glasses with light intensity locked at 1500 lux and will be instructed to wear them for 20–30 min after awakening each morning. The specific timing of use will be established with each participant during the face-to-face session, and will be based on their individual sleep–wake timing and chronotype, accounting for early awakenings. A written light therapy manual covers the key components to be discussed in the face-to-face session.

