### Assessments and outcomes

Table 1 displays the measurements used in this study and the time points at which they will be administered. Screening interviews will be conducted in person during recruitment prior to randomisation. Baseline (week 0), mid-treatment (week 3), post-treatment (week 6), and 3-month follow-up (week 12) questionnaires with self-report measures will be completed online by emailing women a link to a survey on Qualtrics, or via telephone for women who prefer not to complete questionnaires online. Questionnaires completed via Qualtrics will be considered valid if they are completed within ±1 week of the planned time.

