## Discussion

This paper outlines the protocol for the development and evaluation of a novel intervention designed to improve the sleep of women sleep during chemotherapy treatment for BC. The results from this trial will advance the knowledge in this field and may have important clinical implications for how best to treat sleep disturbance and insomnia in this population.

The present trial is one of the first to target sleep complaints among women with BC currently undergoing chemotherapy treatment. Despite rates of sleep disturbance in this population being highest around the time of diagnosis and during treatment [80], most previous intervention studies have been carried out in women who have completed primary treatment for BC. The earlier treatment of sleep complaints is advantageous as it 1) may assist women by improving sleep during cancer treatment, and 2) provides women with evidence-based strategies earlier on in their treatment trajectory which they can continue to use after cancer treatment and into survivorship.

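### The adverse-event definition admits only unanticipated events in the 6-week intervention phase, so foreseeable events and any in weeks 6 to 12 need not be recorded

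*Protocol article*

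**What the plan says.** The operative sentence is in Ethics approval and safety monitoring: "A description of all undesirable and unanticipated events during the intervention phase (adverse events) will be recorded on Qualtrics". The bracketed term makes this the article's definition of an adverse event. The same section foresees no serious harm, makes the DSMB responsible for participant safety, and provides that a woman's clinical team is told of severe sleep, depression or anxiety symptoms.

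The intervention phase is fixed elsewhere. The light component is "daily use of light glasses for the 6-week duration of the intervention" (Light therapy individualised protocol). The assessment schedule runs longer: "Baseline (week 0), mid-treatment (week 3), post-treatment (week 6), and 3-month follow-up (week 12) questionnaires" (Assessments and outcomes). The abstract says what the last assessment holds: "There will be 3-month follow-up measurements of insomnia symptoms, fatigue, sleep-related impairment, sleep disturbance, depression and anxiety".

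Only one contact is described as asking about adverse events: a brief call to CBT+ women at the end of the intervention (CBT+ intervention). TAU+ women have a week-4 call to check in and take questions or complaints (TAU+ intervention). No adverse-event question is described for that call.

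**The concern.** Expectedness is normally a label given to an event once it is recorded. Here it is a condition for being recorded at all. The events most plausibly caused by an intervention are often the foreseeable ones, so the definition tends to screen out what a harms record is meant to show.

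The time limit works in the same direction. Benefit is followed to week 12 to see whether it lasts, while adverse-event recording, as described, ends with the intervention phase.

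At stake is what a low count would mean. The article looks ahead to use in routine care and to a larger trial. With this definition, few recorded events could mean few harms, or harms that did not qualify for recording, and the data could not tell these apart.

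**Working it through.** The article gives no figure to reproduce. The check sets its statements side by side.

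**1. The two conditions.** The sentence joins two adjectives with *and* before a single noun. There are two ways to read it:
- *Both must hold.* An undesirable but foreseeable event is then not an adverse event.
- *Either suffices.* A pleasant surprise would then also be an adverse event, since it is unanticipated. That is not a sensible meaning.

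The first reading is the natural one. Nothing elsewhere widens it: the end-of-intervention call asks about adverse events but does not redefine the term.

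**2. What might be foreseeable.** The article has no list of anticipated harms. Two places hint at some:
- Screening excludes women "having a history of migraines" but gives no reason.
- The background on light therapy says morning light should come early "without forcing individuals to wake too early resulting in daytime sleepiness". This is a general remark on timing, not a harm predicted for this regimen.

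Headache, eye symptoms and daytime sleepiness are therefore reasonable examples of foreseeable events, but they are inferred.

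**3. The window.** The inputs are a 6-week intervention and a last assessment at week 12.
- Weeks with adverse-event recording described: 0 to 6, so 6/12 = 50% of scheduled time.
- Weeks without it: 6 to 12, so (12 − 6)/12 = 50%.

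**4. What is still seen after week 6.** The follow-up scales cover insomnia symptoms, fatigue, sleep-related impairment, sleep disturbance, depression and anxiety. Worsening in any of these can be compared between arms at week 12. The text describes no measure of headache or eye symptoms. Table 1 is not legible in the copy reviewed, so an item there cannot be ruled out.

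**5. How many women a change could still reach.** Recruitment ended in October 2019 and the protocol version is dated 18 November 2019 (Trial status). Taking week 0 as close to randomisation:
- Week 12 was still to come on that date for women who started after 18 November minus 84 days, which is 26 August 2019.
- Week 6 was still to come for women who started after 18 November minus 42 days, which is 7 October 2019.

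The article does not say how many of the 101 randomised women these are. With recruitment open from July 2018, most of the recruitment period lies before both dates.

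**The case against.** The strongest reply has four parts.

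*The wording is loose rather than restrictive.* Staff may have recorded every undesirable event whatever the sentence says. That is possible, but the sentence states a rule and no other text relaxes it. A different practice would be a reason to correct the sentence.

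*The window matches planned exposure.* The glasses are prescribed for 6 weeks only, and the remark in the Discussion that women gain strategies "which they can continue to use after cancer treatment and into survivorship" is a rationale, not a treatment schedule. This stands as far as exposure goes. It does not cover events that begin late or persist.

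*This is a condensed article.* The full protocol may hold an expectedness list or later safety contacts. This is fair for anything merely absent, and the missing list is not criticised here. The definition and its time limit, however, are stated text.

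*Harms are visible by other routes.* This stands in part, and it rules out three stronger readings that a reader might infer:
- That the protocol discards harms it has itself named. It names none.
- That nothing is collected between weeks 6 and 12. The week-12 scales are collected, and the rule on severe symptoms carries no time limit.
- That the DSMB would see no harms. Its remit is participant safety in general, not only adverse events as defined.

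**Conclusion.** The point holds in a limited form. As written, the definition lets undesirable but foreseeable events go unrecorded, and adverse-event recording is described for only half of the 12 scheduled weeks.

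The conclusion on foreseeable events assumes the natural reading of the sentence. The conclusion on the window does not depend on that reading. No count of lost events can be given, because the article states neither a rate nor a list. A figure such as zero capture of treatment-related harms would go beyond the text.

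The primary and secondary efficacy analyses are untouched. The weakness is confined to the harms record. It matters most for events with no described scale, such as headache or eye symptoms, and less for sleep, fatigue, daytime impairment and mood.

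**What to change.** In Ethics approval and safety monitoring, define an adverse event as any undesirable event after randomisation, whether or not anticipated. Classify expectedness and relatedness afterwards, as attributes of the recorded event. Extend the window to the week-12 assessment. Put one identical adverse-event item to both arms at the assessments that remain, because the only enquiry described as asking about adverse events is for CBT+ alone.

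For women who have already completed, report the definition and window actually applied and make no safety claim beyond them.

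The cost is a changed definition, one questionnaire item, and notice of the change to the ethics committee and participants, as the article already requires for modifications. There are two real downsides. More events will be recorded in both arms, many of them chemotherapy effects; the randomised control arm gives the background rate against which to read them. Ascertainment will also differ between earlier and later participants, so the report should show events separately for the two periods and not pool them without comment.
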